### Sample size

With the proposed total sample size of 390 (130 per condition), we have sufficient power (80%) to detect a small to medium treatment effect (Cohen’s D = 0.39) of either CaCBT or CulFI over TAU on PANSS total score at post-treatment (3-month). The selection of effect size has been informed by a meta-analysis of culturally adapted psychosocial interventions [34] and effect sizes generated from meta-analysis of CBT for psychosis [35]. Cohen’s D of 0.39 is also equivalent to a clinically meaningful reduction in PANSS of 6.70 points. The standard deviation, informed by our pilot work, was taken as 17.18 [26]. For sex or gender-based subgroup analysis, the minimum detectable effect sizes to attain sufficient power increase to 0.48 and 0.67 for men and women respectively. Our exploratory analysis will compare the effect of CulFI with CaCBT in improving patient and carer related outcomes. Although this exploratory outcome is not adequately powered for a non-inferiority analysis, it will inform sample size for future comparative clinical trials. The power calculation has considered 20% attrition at post treatment and was based on an end-point analysis. Longitudinal analysis will be more powerful with reduction in measurement error due to repeated measures.

### Statistical analysis

Descriptive analysis will first be conducted for the baseline data to inspect group differences across the three conditions. Patterns of missing outcome data will be examined as a function of recorded baseline characteristics and patterns of compliance with the protocol. For the primary and secondary aims, linear mixed-effects models will be the main analytic strategy and will be conducted under an intention-to-treat framework. A multiple imputation approach will be employed as the missing data method to account for potential bias caused by attrition. Two types of analysis will be conducted to evaluate the treatment effects of CaCBT and CulFI compared to TAU. An endpoint analysis will focus on the pre-post difference at 3 months and a longitudinal analysis will inspect change overtime (baseline, 3 months, and 6 and 12-months post intervention) regarding long-term effect and sustainability. Treatment assignment and its interaction with time will serve as the primary predictors with site, key demographics and baseline outcome measure being controlled as covariates. For moderation analysis concerning biological sex and gender, we will include interaction between treatment assignment and sex and gender in the endpoint analysis and add time to form three-way interaction in the longitudinal analysis. Moderation effects of sex and gender will be assessed in separate models so their effects can be estimated independently. Similar approaches will be applied for secondary outcomes and generalized linear mixed effects models will be in place for binary outcomes. For the exploratory aim to compare effect of CaCBT and CulFI in improving patient and carer related outcomes, we will conduct noninferiority tests to evaluate if the difference between CaCBT and CulFI is within the noninferiority margin for each individual outcome. The noninferiority margins will be determined carefully following well-accepted guidelines [36] and clinical knowledge.

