### Randomization and masking

Participants (i.e., patients) will be randomised using a secure web-based randomization system. Participants will be allocated to trial groups using permuted block with variable block sizes stratified by site and sex. We have not included additional stratification variables as per best practice in RCTs [33]. We will assess other potential prognostic characteristics (age, duration of illness, gender, sex) in our a priori subgroup analyses. Therapists will contact the participant within 1 week of randomization to inform them about treatment allocation. The time and date of sessions will be set based on the participant’s preference. Participants randomized to the CaCBT group are patients who will receive 12 individual sessions from a trained Masters level research psychologist over 12-weeks. Each session will last for 60 min. Participants in the CulFI group consist of patients and their carers who will receive 10 sessions of 40–60 min, delivered weekly for the first 8 weeks and fortnightly for the remaining 4 weeks. All sessions will be delivered by trained therapists who will receive two months training from senior therapists before starting intervention. The third group will receive TAU. Assessments will be carried out at baseline, months 3, 6, and 12. These scales will be administered in-person and/or via secure videoconference software by trained, blinded research analysts (RAs). This is an assessor masked RCT and due to the nature of the interventions it will be impossible to mask clinicians in participating centres or the participants themselves allocated to the interventions. Participants will be asked before assessments not to reveal any information about treatment to assessors. To avoid unmasking, outcome assessors will be located separately from treatment providers, and we will assign new outcome assessors in cases of unintentional unmasking. Statistical analysis will be partially masked (using treatment group but not what each group is).

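### The stated 80% power makes no allowance for therapist clustering in the two active arms, and the listed model terms include no therapist effect

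*Protocol article*

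**What the plan says.** **Delivery.** The sections on the study interventions give CaCBT as 12 individual sessions with a research psychologist and CulFI as 10 sessions for patients and carers. Under Randomization and masking: "All sessions will be delivered by trained therapists who will receive two months training from senior therapists before starting intervention". The Treatment-as-usual section describes medication and physician follow-up, with no study therapist. The number of therapists is not stated, nor whether a therapist works in one active arm or both.

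**Power.** Under Sample size, the claim for 130 patients per arm is that "we have sufficient power (80%) to detect a small to medium treatment effect", at d = 0.39, for either active arm over TAU at three months. The effect is described as "equivalent to a clinically meaningful reduction in PANSS of 6.70 points", and the standard deviation, "informed by our pilot work, was taken as 17.18". One adjustment is named: "The power calculation has considered 20% attrition at post treatment and was based on an end-point analysis". No ICC or design effect appears.

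**Model.** Under Statistical analysis, "linear mixed-effects models will be the main analytic strategy and will be conducted under an intention-to-treat framework". The predictors are treatment and its interaction with time; the covariates are site, key demographics and the baseline value of the outcome. No random effects are listed.

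**The concern.** Patients who share a therapist share that therapist's skill and style, so their outcomes may be correlated. Here this can happen in CaCBT and CulFI but not in TAU, which makes the design partially nested. Two things follow.

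First, the mean of an active arm is less precise than the same number of independent patients would make it, so a power calculation that treats patients as independent is too favourable on its own terms. Second, a model without a therapist term reports standard errors that are too small for each active-versus-TAU contrast, so intervals are too narrow and the error rate exceeds its nominal level. These are the primary comparisons of a trial meant to confirm efficacy.

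**Working it through.** **Inputs from the Sample size section:** 130 per arm; 20% attrition, so 130 × 0.8 = 104 analysed; difference 6.70; SD 17.18; d = 6.70/17.18 = 0.390. **Assumed, because not stated:** two-sided 5% per contrast; k = 5, 10 or 20 therapists per active arm; ICC = 0.01, 0.05 or 0.10; equal caseloads; equal total variance in all arms; normal approximation.

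**Step 1: reproduce the plan's figure.** n = 2 × ((1.960 + 0.842)/0.39)² = 103.2, so 104 per arm; 104/0.8 = 130. With SE = √(2/104) = 0.1387 SD, power = Φ(0.39/0.1387 − 1.96) = Φ(0.852) = 80.3%. The stated 130 is recovered exactly with a design effect of 1. It contains no therapist allowance and almost no slack.

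**Step 2: add partial nesting.** Caseload m = 104/k. Design effect in an active arm DE = 1 + (m − 1) × ICC; TAU keeps 1. For active versus TAU, SE = √((DE + 1)/104), and the variance factor is F = (DE + 1)/2.

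With k = 10 and ICC = 0.05:
- m = 10.4; DE = 1 + 9.4 × 0.05 = 1.47; F = 1.235; SE = 0.1541, which is √1.235 = 1.11 times the value in step 1.
- Power = Φ(0.39/0.1541 − 1.96) = Φ(0.571) = 71.6%.
- Type I error if clustering is ignored = 2 × (1 − Φ(1.96/1.111)) = 7.8%.
- Detectable effect at 80% power = 2.802 × 0.1541 = 0.43 SD.

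**Step 3: the range, each active arm versus TAU, no baseline adjustment.**

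| Therapists per arm | ICC | Power at d = 0.39 | Type I error if ignored | Detectable effect (SD) |
|---|---|---|---|---|
| 5 | 0.01 / 0.05 / 0.10 | 76.5% / 63.3% / 51.3% | 6.2% / 10.9% / 16.5% | 0.41 / 0.48 / 0.55 |
| 10 | 0.01 / 0.05 / 0.10 | 78.5% / 71.6% / 64.0% | 5.5% / 7.8% / 10.6% | 0.40 / 0.43 / 0.47 |
| 20 | 0.01 / 0.05 / 0.10 | 79.5% / 76.3% / 72.5% | 5.2% / 6.2% / 7.5% | 0.39 / 0.41 / 0.43 |

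Allowing for the few therapists with approximate Satterthwaite degrees of freedom, the power figures for 10 per arm become 75.9% / 68.1% / 59.8%.

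**Step 4: does the site covariate remove it?** No. A site effect is common to all three arms at a centre and cancels from the within-site contrast. Therapist variation is present in the active patients and absent from the TAU patients, so it stays in the contrast. A simulation with site fixed effects and no therapist term (10 patients per arm per site, ICC 0.05, 4,000 runs) gave 7.2% against TAU. Its Monte Carlo standard error is √(0.072 × 0.928/4000) = 0.4 points, so it agrees with 7.8%.

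**Step 5: does baseline adjustment remove it?** It can recover power. With k = 10 and ICC 0.05, if adjustment scales all variance by 1 − r², 80% is restored when 1 − r² = 1/1.235, so r is about 0.44. If it cannot reduce the therapist part, which arises after randomisation, the condition is 2(1 − r²) + 0.47 = 2, so r is about 0.48. It does not correct the standard error. At r = 0.5 with the therapist part untouched, the residual ICC is 0.05/0.75 = 0.067, DE is 1 + 9.4 × 0.067 = 1.63, F is 1.31, and type I error if ignored is 2 × (1 − Φ(1.96/√1.31)) = 8.7%.

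**The case against.** Three stronger readings are tempting, and the document does not support them.

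**That the standard errors are too small.** The article names a mixed model but lists no random effects at all, not even the patient effect that the longitudinal analysis would need. The absence of a therapist term from a list of predictors and covariates does not show that one is excluded, and random-effects structure is commonly left to an analysis plan, which is not shown. This stands, so the statement about standard errors must be conditional.

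**That the 80% is overstated for the planned analysis.** The sample size reproduces as an unadjusted endpoint comparison, while the planned model adjusts for baseline PANSS. In the middle case a baseline correlation of about 0.44 to 0.48 offsets the clustering. The article gives no such correlation and does not say whether 17.18 is an unadjusted SD, so the net direction is unknown. This also stands. What remains is that the 80% rests on independence that the design does not provide.

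**That CaCBT versus CulFI is affected even more.** That would require separate therapists in each arm. If they are shared, much of the therapist effect cancels. The contrast is also an exploratory noninferiority comparison, which the Sample size section itself calls not adequately powered. No error rate is claimed for it here.

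It is also fair to say that the size depends on unstated quantities: at an ICC of 0.01 with 20 therapists per arm the effect is negligible.

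**Conclusion.** The point holds in conditional form. The nesting is a fact of the design, and the power calculation demonstrably contains no allowance for it; neither conclusion depends on an unseen analysis plan. On the unadjusted basis that the article uses, every combination examined takes power below 80%, from 79.5% down to 51.3%. The middle case of 10 therapists per arm and ICC 0.05 gives 71.6%. If the listed terms are the full model, type I error for each active arm against TAU would be 5.2% to 16.5% over the same range, and 7.8% in the middle case.

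Therapist count and ICC are assumptions, so no single corrected figure follows from the document. The 80% should be called unsupported rather than wrong. The matter deserves correction because it touches the primary contrasts and costs little to settle.

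**What to change.** 1. **Data.** Record the treating therapist's ID for every CaCBT and CulFI patient. The planned supervision and review of recorded sessions already need it. Record also whether a therapist works in both arms.
2. **Model.** Specify a partially nested mixed model: a random therapist intercept in the active arms only, TAU patients treated as independent, site kept as a fixed effect, baseline adjustment as planned, and a small-sample degrees-of-freedom correction such as Kenward-Roger. If there is only one therapist per arm at each centre, say that therapist and centre-by-treatment variation cannot be separated.
3. **Sample size section.** Keep enrolment at 390. Restate power or the detectable effect with an assumed therapist count, ICC and baseline correlation, over a range. Without baseline adjustment, 10 therapists per arm and ICC 0.05 give about 0.43 SD in place of 0.39.

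The cost is one data field and a few lines of text. The downside is slightly wider intervals and a less favourable stated power.

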### Study objectives

To determine the clinical efficacy of CaCBT and CulFI compared to TAU on reducing overall symptoms of psychosis in patients with FEP in Pakistan.To determine the efficacy of CaCBT and CulFI compared to TAU on positive and negative symptoms of psychosis, general psychopathology, depressive symptoms, quality of life, general functioning, and insight in patients with FEP in Pakistan.To determine the efficacy of CaCBT and CulFI compared to TAU on improving carer experience, carer wellbeing, carer illness attitudes and symptoms of depression and anxiety in family and carers of patients with FEP in Pakistan.To determine the comparative effect of CaCBT and CulFI in improving patient and carer-related outcomes in individuals with FEP in Pakistan.To estimate the cost-effectiveness of delivering culturally appropriate psychosocial interventions in low-resource settings.To explore delivery and reach of each intervention, tolerability of intervention components, acceptability of interventions, understanding mechanism of change and developing an understanding of barriers and facilitators to future adoption using process evaluation.

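### CaCBT and CulFI are to be compared by formal non-inferiority tests on every outcome, although the protocol calls this comparison exploratory and underpowered and does not require the reference arm to beat TAU

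*Protocol article*

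**What the plan says.** The fourth study objective is "To determine the comparative effect of CaCBT and CulFI in improving patient and carer-related outcomes". The Statistical analysis section turns this into a formal test: "we will conduct noninferiority tests to evaluate if the difference between CaCBT and CulFI is within the noninferiority margin for each individual outcome". Margins are to be set later from guidelines and clinical knowledge.

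The Sample size section describes the same comparison differently. It calls it exploratory, states that "this exploratory outcome is not adequately powered for a non-inferiority analysis", and gives its purpose as helping to plan the size of later head-to-head trials.

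Both interventions are also compared with a concurrent TAU arm. That comparison is the primary question, and the one for which the sample was sized.

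**The concern.** The two sections do not fit together. One announces a test that ends in a verdict for each outcome. The other says the sample is too small for that kind of test and gives a purpose that needs an estimate and its precision, not a verdict.

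The more serious gap is interpretive. A non-inferiority finding means something only if the reference treatment works in the trial at hand. Whether CaCBT and CulFI beat TAU in this setting is what the trial sets out to learn, and nothing stated ties the non-inferiority conclusion to that result. Followed as written, the plan would allow two arms that both fail against TAU to be reported as non-inferior.

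The scope enlarges the problem. The first three objectives name overall symptoms, seven further patient outcomes and four or five carer outcomes (depending on whether depression and anxiety are counted together). That makes 12 or 13 separate verdicts. An inconclusive test is also easily misread as evidence that one therapy is worse.

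**Working it through.** **Inputs (Sample size section).** 390 patients, 130 per arm. Power: "we have sufficient power (80%) to detect a small to medium treatment effect". Effect over TAU: "Cohen’s D of 0.39 is also equivalent to a clinically meaningful reduction in PANSS of 6.70 points". SD: "The standard deviation, informed by our pilot work, was taken as 17.18". Attrition: "The power calculation has considered 20% attrition at post treatment and was based on an end-point analysis". Evaluable per arm: 130 × 0.80 = 104.

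**Assumptions, because the article gives no figure.** Alpha is two-sided 0.05 for superiority and one-sided 0.025 for non-inferiority, with one-sided 0.05 also shown. The two therapies are truly equal. The margin is an illustrative fraction of the 6.70-point effect.

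**1. The plan's own figure.** 6.70 / 17.18 = 0.39. n = 2 × (1.960 + 0.842)² / 0.39² = 103.2, so 104 per arm. 104 / 0.80 = 130 per arm and 390 in total. The stated size is reproduced for superiority over TAU.

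**2. Precision of CaCBT minus CulFI.** SE = 17.18 × √(2/104) = 2.38 points. The 95% half-width is 1.960 × 2.38 = 4.67 points, or 0.27 SD.

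**3. Power for non-inferiority.** Power = Φ(margin / SE − z).
- Half the effect, 3.35 points: Φ(1.406 − 1.960) = 29%. At one-sided 0.05: Φ(1.406 − 1.645) = 41%.
- Two-thirds of the effect, 4.47 points: 47% at one-sided 0.025.
- For 80% power at 3.35 points: n = 2 × 17.18² × (1.960 + 0.842)² / 3.35², so 413 evaluable. 413 / 0.80 gives 517 randomised per arm.

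**4. Smallest margin with 80% power.** (1.960 + 0.842) × 2.38 = 6.67 points. As a share of the assumed effect over TAU, 6.67 / 6.70 = 99.6%. A margin of that size preserves almost none of the effect.

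**5. Sensitivity.** The planned model adjusts for the baseline outcome, which multiplies the SD by √(1 − r²). The correlation r is not given, so a range is shown.

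| Setting | Power at 3.35 points | Smallest margin with 80% power |
|---|---|---|
| Unadjusted, one-sided 0.025 | 29% | 6.67 |
| Unadjusted, one-sided 0.05 | 41% | 5.92 |
| All 130 per arm evaluable, one-sided 0.025 | 35% | 5.97 |
| r = 0.3, one-sided 0.025 | 31% | 6.37 |
| r = 0.5, one-sided 0.025 | 37% | 5.78 |
| r = 0.7, one-sided 0.025 | 50% | 4.77 |

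**6. What the test does not look at.** The formula in step 3 contains the margin, the SD, the sample size and the difference between the two therapies. It does not contain the effect of either over TAU. If neither therapy does anything, their difference is also zero. The chance of a non-inferiority verdict is then the same as when both work equally well: 29% at 3.35 points and 80% at 6.67 points (unadjusted, one-sided 0.025).

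**The case against.** The strongest reply is that the article has already been candid. It labels the comparison exploratory in both sections, admits the lack of power and limits the purpose to informing later trials. It plans no confirmatory claim. That stands, and it holds the severity down. It does not explain why a verdict is planned when the stated purpose needs only an estimate.

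A reader might go further than the documents allow in four ways.

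- **That the margins and the reference arm are missing.** The article condenses a fuller protocol, and an analysis plan may exist that is not shown. Leaving these details to it is normal, and their absence here is not the defect.
- **That no prior effect exists from which to derive a margin.** The Background cites meta-analyses of both therapies, the Sample size section draws its effect size from meta-analyses, and the Discussion says each therapy has been shown to improve outcomes. Evidence from low-resource settings is described as scarce. That weakens a margin but does not rule one out. The concurrent TAU arm also lets the trial check whether the reference works. What is lacking is a rule that uses the check.
- **That no sensible margin could be supported.** The article fixes neither margin nor alpha, and baseline adjustment helps: at r = 0.7 a margin of 4.77 points (71% of 6.70) has 80% power. No SD is given for any outcome other than PANSS total, so nothing numerical can be said about the carer outcomes.
- **That the test is really one of equivalence.** Speaking of a difference lying within a margin is loose, but the article says non-inferiority throughout, and the phrase can be read one-sidedly.

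It is also fair to say that a non-inferiority analysis produces the difference and its interval anyway. The change therefore concerns what is concluded and reported more than what is computed.

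**Conclusion.** The point holds in limited form. The article plans formal non-inferiority tests on every patient and carer outcome for a comparison that it describes as exploratory and not adequately powered for them. It states no condition that the reference arm must first beat TAU.

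On PANSS total at 3 months, power at a half-effect margin is 29% unadjusted, 41% at one-sided 0.05, and 31% to 50% with baseline adjustment at r from 0.3 to 0.7. The smallest margin with 80% power runs from 6.67 points down to 4.77 across the settings shown, against an assumed effect over TAU of 6.70.

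These figures rest on the article's SD and attrition and on the assumed alpha, equal arms, illustrative margins and correlations. The sample size and the primary comparisons with TAU are unaffected. Severity is minor to moderate.

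**What to change.** In the Statistical analysis section, replace the non-inferiority tests with the CaCBT minus CulFI difference and its two-sided 95% confidence interval for each outcome, taken from the same mixed model. Keep it exploratory, and state that no non-inferiority or equivalence claim will be made. This answers the fourth objective directly and gives later trials the estimate and precision they need.

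If one test is kept, limit it to PANSS total at 3 months. Name one reference arm, fix the margin before unmasking, and interpret the result only if that arm beats TAU in this trial.

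The cost is a change of wording in the protocol and analysis plan, with no new patients or data. The sponsor gives up a formal non-inferiority verdict.

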#### Frequency of analysis

There are no planned interim analyses for efficacy. These will only be carried out if requested by the data monitoring committee. All main statistical analyses will be based on the Intention-to-Treat principle. Analysis will take place after full recruitment and follow-up. During the trial, periodic quality checks of data will be carried out by the trial statistician masked to treatment allocation. Once data entry has been completed preliminary data analysis will be carried out whilst maintaining masking to treatment allocation. The trial will be conducted and reported as per CONSORT recommendations for RCTs.

